### Statistical analysis plan

Statistical methods for inference in small samples will be used according to a statistical analysis plan. The minimum number of HCPs per APO audit cycle has been estimated based on the assumption that each HCP will register about 25 cases, including either consultations or dispensations, during the audit registration. A decrease of 15% in antibiotic prescribing can be expected after the intervention (from about 40% before to about 25% after). The within-practice correlation coefficient is 0.1. If the comparison is to be performed at the 5% level of significance (two-sided) with 80% power, then the number of HCPs to be included should be 25 per APO cycle. There will be 20 APO cycles in the project (one for each of the 4 healthcare settings involved in each of the 5 target countries). We assume the participation of 500 HCPs in the project and the registration of 25,000 cases.

We will apply the Fisher exact test to the frequencies of prescriptions before and dispensations before and after the audit for each group of professionals and setting/country to test the null hypothesis of no effect of the audit. We will also estimate the effect of the interventions with logistic two-level regression models: a) cases of CAIs and b) HCP participants. Antibiotic prescription will be considered as the dependent variable (yes/no) as well as the concepts of inappropriate prescribing and inappropriate dispensing. These models control for symptoms and duration, as well as for the demand for antibiotics by the patient. Goodness of fit will be assessed using the Wald test of the model, with the deviance test to compare alternative models. Statistical significance will be considered with *P* < 0.05. The data will be analysed using Stata v16.

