### Phase 2: audit registrations

The project will conduct two audit registrations: the first will begin before the intervention (February 2022) and the second will take place after the intervention (February 2023). The same month has been chosen for the implementation of both registrations to minimize the effect of potential seasonal variation in CAIs. A registration pilot testing, in November 2021 with approximately five HCP participants per setting and per country, ensured that the content of the registration chart was relevant to their practice and easily understood, and confirmed that sufficient patients could be recruited.

During the audit period the participants will use the APO registration chart to record all consultations or dispensations regarding the CAIs selected for audit. Participants will be asked to fill in the chart with the consecutive consultations they receive regarding the CAIs selected, and in the case of pharmacies, all the systemic antibiotic dispensations given for acute infections. A specific registration chart for each of the 4 settings has been developed considering their characteristics and the quality improvement areas that HAPPY PATIENT seeks in each setting. The example of the template used in nursing homes is depicted in Fig. 2. At most, 10 main domains and a maximum of 45 variables are used to describe the topic investigated. The main domains are lined up in a logical way; for example: type of contact, symptoms present, examinations performed, diagnosis, treatment, and assessment. According to the APO methodology the variables are exhaustive (include all possibilities) and exclusive (no overlapping), and all follow the same logic plan. One line is filled in for each registered case and, as a general rule, only multiple choice is allowed (no open-ended text). At least one choice per main group is needed. A short instruction sheet will be provided for all HCP participants, with details about the registration period, the inclusion and exclusion criteria for the cases and a brief explanation of the content of each main group.

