**Fig. 2 Fig2:**
[figure not shown]
Draft of the template to be used in nursing homes in the HAPPY PATIENT project (patients receiving antibiotics).

Data originating from the registration will be used for quality assessment using quality indicators. In the case of general practice, OOH services and nursing homes, an indicator of antibiotic inappropriateness is considered. Antibiotic prescribing is considered appropriate if it fulfils the following criteria: a) the diagnosis for which this is given might be bacterial; b) it is suspected that the criteria presented by the patient are caused by bacteria; and c) the choice of the antibiotic reflects the local pathogens and resistance patterns in each setting. Anything else is inappropriate. Although antibiotic underprescribing – withholding antibiotic use when the infection is suspected to be of bacterial origin – is also inappropriate, this is negligible in western countries according to the medical literature [18]. Based on the charts used in the registrations the group defined when an antibiotic was appropriate or not. In the case of pharmacies, several indicators have been defined, based on the safety and the appropriate advice given to the patients. Figure 3 describes the example used in OOH services.

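### The 80% power for prescribing falling from 40% to 25% is stated for all 20 audit cycles but cannot apply to the 5 pharmacy cycles, which register only antibiotic dispensations

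*Protocol article*

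**What the plan says.** The Statistical analysis plan section gives a single sample-size calculation. Its unit covers both kinds of record: "each HCP will register about 25 cases, including either consultations or dispensations, during the audit registration". Its effect is "A decrease of 15% in antibiotic prescribing can be expected after the intervention (from about 40% before to about 25% after". The other inputs are "The within-practice correlation coefficient is 0.1" and "If the comparison is to be performed at the 5% level of significance (two-sided) with 80% power", and the result is 25 professionals per cycle. The calculation is then spread over the whole project: "There will be 20 APO cycles in the project (one for each of the 4 healthcare settings involved in each of the 5 target countries". No setting is excepted.

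The section Phase 2: audit registrations describes what is recorded. The general rule is consecutive consultations for the selected infections, with one exception: "in the case of pharmacies, all the systemic antibiotic dispensations given for acute infections". On outcomes, the same section says: "In the case of pharmacies, several indicators have been defined, based on the safety and the appropriate advice given to the patients". The Statistical analysis plan section lists three dependent variables (prescription yes/no, inappropriate prescribing and inappropriate dispensing) without assigning them to settings. It also plans a Fisher exact test on prescription and dispensation frequencies by professional group and setting/country.

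For nursing homes, the caption of Fig. 2 reads "Draft of the template to be used in nursing homes in the HAPPY PATIENT project (patients receiving antibiotics".

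**The concern.** A fall from 40% to 25% needs a denominator that includes patients who received no antibiotic. A register made up only of antibiotic dispensations has none. The power statement therefore attributes to the pharmacy cycles a property they cannot have. The outcomes that pharmacies do have carry no baseline, expected effect or power in the article.

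A reader who takes the statement at face value will believe that each pharmacy cycle was sized for its own question. A null pharmacy result could then be read as a well-powered null, although the effect it was powered to detect was never set out. The Discussion expects improvement in all four settings, so the pharmacy result will be interpreted. The Limitations section says that, to the authors' knowledge, this is the method's first use in community pharmacies, so the effect assumed for prescribing cannot simply be carried over.

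**Working it through.** **Inputs, all from the Statistical analysis plan section:** 40% before, 25% after; two-sided 5%; 80% power; correlation 0.1; 25 cases per professional per audit; 25 professionals per cycle; 20 cycles; totals of 500 professionals and 25,000 cases.

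**1. The plan's own figure.** Treat the two audits as independent samples.
- Cases per audit without clustering: n = [1.96·√(2·0.325·0.675) + 0.84·√(0.40·0.60 + 0.25·0.75)]² / 0.15² = 152; with continuity correction, 165.
- Design effect: 1 + (25 − 1)·0.1 = 3.4.
- Professionals: 152·3.4/25 = 20.7, so 21; with continuity correction 165·3.4/25 = 22.4, so 23.
- Totals: 20·25 = 500 professionals and 500·25·2 = 25,000 cases.

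The stated 25 is close to 23 and slightly conservative. With 25 professionals the effective sample is 25·25/3.4 = 625/3.4 = 184 per audit, which gives about 87% power without continuity correction. The arithmetic is sound.

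**2. The same outcome in a pharmacy cycle.** Each audit would hold about 625 records, every one an antibiotic dispensation. The proportion is 625/625 = 100% before and 625/625 = 100% after. The difference is zero by construction. A two-by-two table of audit by antibiotic yes/no has an empty column, so a Fisher test on it says nothing.

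**3. Size.** 5 of 20 cycles; 5·25 = 125 of 500 professionals; 125·25·2 = 6,250 of 25,000 cases. Each is 25% of the project. At most 15 cycles (375 professionals, 18,750 cases) can carry the sized outcome.

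**4. What 25 professionals give for a yes/no pharmacy indicator.** The article gives no baseline or effect, so both are assumed, and the correlation of 0.1 is carried over.
- Detectable difference at a 50% baseline: (1.96 + 0.84)·√(2·0.25/184) = 2.80·0.0521 = 0.146, about 15 points.
- Power with 184 effective cases per audit, by assumed baseline:

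| Fall | 20% | 30% | 40% | 50% | 60% | 70% | 80% | 90% |
|---|---|---|---|---|---|---|---|---|
| 15 points | 99% | 93% | 87% | 83% | 82% | 85% | 90% | 97% |
| 10 points | 77% | 60% | 52% | 49% | 49% | 52% | 60% | 77% |
| 5 points | 24% | 19% | 17% | 16% | 16% | 17% | 21% | 30% |

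Whether a pharmacy cycle reaches 80% power therefore depends on an effect size that the article does not give.

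**The case against.** Three points can be made for the plan.

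*Pharmacies have their own outcomes.* This stands. A reader might infer that the pharmacy cycles have nothing to analyse, or that a prescription yes/no model will be run there. The article supports neither. It gives pharmacies safety and advice indicators and lists inappropriate dispensing as a dependent variable, and these can vary among dispensations. The fault lies in the power statement, which was calculated for a different outcome.

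*The sample size still works.* This largely stands. For a 15-point change in a yes/no indicator, 25 professionals give at least about 82% power across the assumed baselines. A reader might infer that too few pharmacists are recruited, but nothing in the article shows that. What remains is that no pharmacy effect is stated, and a 10-point change would have only 49% to 77% power.

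*The detail belongs in the separate statistical analysis plan,* which the article mentions and which is not shown. Assigning outcomes to settings may well be there. That does not rescue a statement in the article that contradicts its own registration rule.

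A stronger reading would add nursing homes, making 10 cycles, or half the project. It rests only on the parenthesis in the Fig. 2 caption. That caption describes a draft, the figure is not shown, and it may depict one part or version of the chart. The registration rule asks for consecutive consultations and excepts pharmacies alone, and nursing homes share the inappropriateness indicator with general practice and out-of-hours services. The caption and the rule need reconciling; a missing outcome in nursing homes is not established.

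**Conclusion.** The concern holds for the 5 pharmacy cycles: 125 professionals, 6,250 cases, a quarter of the project. There the 40%-to-25% outcome cannot be formed, and the stated 80% power does not refer to any outcome those cycles have. This follows from the article's own text and needs no assumption.

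The replacement figures do rest on assumptions: a yes/no indicator counted per dispensation, baselines from 20% to 90%, the correlation of 0.1 carried over to pharmacies, and audits treated as independent although the same professionals take part in both. On that basis a change of about 15 points is detectable at a 50% baseline, and smaller changes are underpowered. The calculation itself is correct for settings that register untreated cases.

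**What to change.** - Limit the 40%-to-25% power statement, and the prescription yes/no analysis, to settings that register untreated cases.
- For pharmacies, name one safety, advice or inappropriate-dispensing indicator, counted per dispensation, as the tested outcome. State its detectable difference with 25 professionals, 25 cases each and correlation 0.1: about 15 points at an assumed 50% baseline, with about 49% to 77% power for a 10-point fall at baselines of 20% to 90%. Fix the choice before the two audits are compared.
- For nursing homes, state whether untreated patients are registered, so that the Fig. 2 caption and the registration rule agree. If only treated patients are registered, the same restriction applies there and the power statement covers 10 cycles.

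The cost is a few sentences in the sample-size and outcome text. Recruitment and the pharmacy chart stay as they are. Changing who is registered in nursing homes is not proposed: the need is not shown, and a change between audits would break the before/after comparison.

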### Design

HAPPY PATIENT was initiated in January 2021 and the project is planned to finish in December 2023. The project includes 15 partners from nine countries, as indicated in Table 2. The Audit Project Odense (APO) methodology is used [15], which is an evidence-based multifaceted intervention to improve quality of care by implementing guidelines [16]. This is a before and after intervention study, with two audit registration periods (Fig. 1). A minimum number of 25 HCPs will be recruited in each setting and will collect CAIs during a first audit registration in February 2022. In autumn 2022, the four groups of HCPs will be invited to a face-to-face meeting to receive a multifaceted intervention. In February 2023, the same participants will register the same type of CAIs for a second audit.

**Table 2 Tab2:** Partners in HAPPY PATIENT

Participant organisation name	Abbreviation	Role
Institut Català de la Salut and Fundació Institut Universitari per a la Recerca a l’Atenció Primària de Salut Jordi Gol	ICS/IDIAP	Coordinator of the project. Spanish network
University of Copenhagen	UCPH	Co-design and consensus methodology
Research Unit for General Practice Odense	RUPO	APO methodology. Primary healthcare settings
NORCE Norwegian Research Centre AS	NORCE	Out of hours settings
The Capital Region of Denmark	CAPREG	Nursing homes settings
Rijksuniversiteit Groningen, The Netherlands	RUG	Pharmacy settings
University of Las Palmas de Gran Canaria and Fundación Canaria Parque Científico Tecnológico	ULPGC/FCPCT	Analysis and evaluation of the results
Spanish Society for Family and Community Medicine	SEMFYC	Dissemination and training in communication skills
Nice University Hospital	CHUNICE	French network
Ltd Mano Seimos Gydytojas (My Family Doctor)	FDC	Lithuanian network
Medical University of Lodz, Poland	MUL	Poland network
University of Crete, Greece	UOC	Greek network
European Association for Clinical Pharmacology and Therapeutics	EACPT	Advisor
Rennes University Hospital, France	CHURE	Advisor
University Institute for Patient Care, Spain	UIC	Advisor

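### The Fisher exact test that decides on no effect ignores the clustering of 0.1 used to size the study; its true error rate at nominal 5% is about 3% to 28%, depending on an unstated between-audit correlation

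*Protocol article*

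**What the plan says.** All of the relevant text is in the protocol article, in the Statistical analysis plan and Design sections.

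- **Sizing.** It is assumed that "each HCP will register about 25 cases, including either consultations or dispensations, during the audit registration", with prescribing falling "from about 40% before to about 25% after". The clustering assumption is explicit: "The within-practice correlation coefficient is 0.1". With a two-sided 5% level and 80% power, the protocol arrives at 25 HCPs in each cycle.
- **Test.** "We will apply the Fisher exact test to the frequencies of prescriptions before and dispensations before and after the audit", carried out "for each group of professionals and setting/country to test the null hypothesis of no effect of the audit".
- **Model.** The next sentence adds two-level logistic regression, with cases within HCPs, to estimate the effect of the interventions.
- **Threshold.** P < 0.05 is set for the study as a whole. The text does not say whether the Fisher test or the model decides.
- **Repeat measurement.** The Design section says that "the same participants will register the same type of CAIs for a second audit", a year after the first.

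No figure is given for how strongly an HCP's rate in the first audit predicts the same HCP's rate in the second.

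**The concern.** The sample size allows for clustering and the named test does not. A Fisher test on a two-by-two table of pooled cases assumes that each case is an independent draw. Under the protocol's own assumption, cases from one HCP resemble one another, and each HCP contributes to both columns of the table. The first feature makes the before-after difference more variable than Fisher assumes; the second makes it less variable. Only if the two happen to cancel is the nominal 5% correct.

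At stake are the P values by setting and country, since this is the test attached to the null hypothesis. There are 20 cycles. If no cycle had an effect, a valid 5% test would flag 20 × 0.05 = 1 on average. At an error rate of 27% the expected number is 20 × 0.27 = 5.4. At 16% to 18% it is 3.2 to 3.6.

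**Working it through.** **Inputs from the protocol article.** Rates 40% and 25%; m = 25 cases per HCP per audit; k = 25 HCPs per cycle; correlation ρ = 0.1; two-sided 5%; 80% power; same HCPs in both audits.

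**Assumptions.** The correlation of 0.1 applies to cases within an HCP. The table pools one whole cycle, 25 × 25 = 625 cases per audit. The between-audit correlation r is unknown, so it is varied from 0 to 1.

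**Step 1: the plan's own figure.** For two independent proportions with mean 0.325,

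n = [1.96·√(2·0.325·0.675) + 0.842·√(0.40·0.60 + 0.25·0.75)]² / 0.15² ≈ 152 cases per audit.

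- Without clustering: 152 / 25 = 6.1, so 7 HCPs.
- Design effect: 1 + (25 − 1)·0.1 = 3.4.
- With clustering: 152 × 3.4 = 516.8 cases, and 516.8 / 25 = 20.7, so 21 HCPs.
- With continuity correction: 165 × 3.4 = 561 cases, and 561 / 25 = 22.4, so 23 HCPs.

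The stated 25 is not reproduced exactly. It is on the safe side (87% power by the same formula), and that is not an error. The useful result is that a figure near 25 arises only if clustering was allowed for.

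**Step 2: true variance of the before-after difference.** Relative to independent cases, under no effect:

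F = 1 + (m − 1)ρ − mρr = 3.4 − 2.5r.

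The term in r is the contribution of measuring the same HCPs twice, and it reduces F. F = 1 at r = 2.4 / 2.5 = 0.96.

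**Step 3: true size of the unadjusted test.** Size ≈ 2·[1 − Φ(1.96/√F)]. This was checked by simulating the Fisher test itself (beta-binomial, 25 HCPs × 25 cases × 2 audits, rate 40%, no effect, 10,000 runs per value).

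| r | F | Normal approximation | Simulated Fisher |
|---|---|---|---|
| 0 | 3.40 | 28.8% | 26.9% |
| 0.5 | 2.15 | 18.1% | 17.5% |
| 0.8 | 1.40 | 9.8% | 8.8% |
| 0.9 | 1.15 | 6.8% | 6.0% |
| 1 | 0.90 | 3.9% | 3.5% |

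Smaller repeat simulations gave 27% to 28% at r = 0, 16% to 18% at r = 0.5 and 3% to 4% at r = 1. At a rate of 25% the results are much the same (26.8%, 17.0%, 9.0%, 6.2%, 2.9%). With a correlation near zero the simulated size is 4.2%, so the excess comes from the clustering.

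**Step 4: a test that respects the HCPs.** A paired t test on the 25 HCP-level differences has simulated size 4.7%, 5.1%, 5.0% and 4.6% at r = 0, 0.5, 0.8 and 1. Its power for 40% against 25% is 84%, 96%, 99.7% and nearly 100%.

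**Step 5: the two-level model.** A single HCP intercept amounts to assuming r = 1: any change in an HCP's rate between audits is treated as case-level noise. A linear analogue of that model (2,000 runs per value, no effect) had size 30%, 19%, 12%, 9% and 4% at r = 0, 0.5, 0.8, 0.9 and 1. A test stratified by HCP had 19% at r = 0.5. The logistic model itself was not simulated.

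**The case against.** The strongest defence is that a cluster-aware analysis is already planned. The two-level model recognises HCPs, and the Fisher test could be read as a simple first look. This stands in part: the criticism of the Fisher P values does not carry over automatically to every P value in the study. But the protocol attaches the null hypothesis to Fisher, gives the model the task of estimation, and has no rule for when the two disagree. As described, with cases and HCPs as its only levels, the model is not a safe fallback either (step 5).

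A second defence is that HCPs may have stable habits. This also stands in part. Repeat measurement lowers the inflation, and at r = 1 Fisher is slightly conservative and wastes the information in the pairing. The inflation disappears, however, only when r is about 0.96 or more, and the audits are a year apart.

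A reader might infer that the protocol fixes an error rate of 9% to 28%, or that measuring the same HCPs twice adds to the inflation. The documents support neither. The 9% end holds only if r is 0.8 or less, a figure the protocol does not give, and the pairing term enters with a minus sign.

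**Conclusion.** The point holds: the named test contradicts the clustering assumption in its own section and does not use the paired design. Its error rate at nominal 5% is about 3% to 28%. Where it falls in that range cannot be known from the protocol, because it rests on r. It is anti-conservative for r below about 0.96 and slightly conservative above. The figures also rest on 25 HCPs with 25 cases each and on reading the stated correlation as applying within an HCP; unequal numbers of cases or smaller professional subgroups would change them.

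The sample size is not in question. With 25 HCPs, a paired HCP-level test exceeds the planned 80% power at every r examined.

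**What to change.** For each setting and country, replace the Fisher test with a paired comparison of each HCP's before and after proportions, by a paired t test or a sign-flip permutation test on the HCP-level differences, reported with a 95% CI. Keep the pooled frequencies as description, without P values.

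Alternatively, name the logistic model as the decisive analysis, provided that it includes an HCP-by-audit random effect or a random audit slope by HCP. Either way, state which single analysis the P < 0.05 threshold applies to.

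The cost is a change of wording in the protocol and the statistical analysis plan and a little analysis work. No new data and no additional HCPs are needed. The change should be made before the before-after comparison is run.

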### Setting and population

We will carry out the audit registrations and monitor the intervention outcomes in five countries (Greece, France, Spain, Poland, and Lithuania) with diverse antibiotic prescription rates. In each country, data will be collected in four different settings: (a) general practice, including GPs and nurses; (b) secondary care, in out-of-hours (OOH) services, including doctors and nurses; (c) tertiary care, with nursing homes, involving doctors and nurses who directly engage patients in relation to the prescribing and use of antibiotics; and (d) community pharmacies, with pharmacists and pharmacy technicians.

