The final findings of this quality improvement project will be submitted to a peer-reviewed journal and will be presented in international scientific conferences. The results will be used to inform public health interventions on appropriate antibiotic prescribing and dispensing. Data from all centres will be analysed together and published as soon as possible. The HCPs participating in the study will receive a summary of the main project findings and the perspectives. All data collected as part of this quality improvement project will be shared for common analyses and presentation to the scientific community through publications and conferences.

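### The two-level model gives too small a standard error if HCPs or practices change unequally between audits, the Wald test cannot show it, and the 25-HCP figure leaves unclear which unit the 0.1 correlation belongs to

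*Protocol article*

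**What the plan says.** All the main statements are in the protocol article, section Statistical analysis plan.

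- Model: "We will also estimate the effect of the interventions with logistic two-level regression models: a) cases of CAIs and b) HCP participants". No practice, home, service or pharmacy level is named, and no audit effect that varies between units.
- Model checks: "Goodness of fit will be assessed using the Wald test of the model", and the same sentence adds a deviance test for comparing alternative models.
- Planning correlation: "The within-practice correlation coefficient is 0.1". The same paragraph plans about 25 cases per HCP and 25 HCPs per audit cycle, for a fall in prescribing "from about 40% before to about 25% after" at the "5% level of significance (two-sided) with 80% power".

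Three other sections bear on this. Design has the same HCPs register in both audits. Setting and population lists more than one profession in each setting, for example "general practice, including GPs and nurses". Table 1 gives group practice as the organisation of primary care, or one form of it, in all five countries. Ethics and dissemination has each record coded by HCP and a running number, and mentions no site code.

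**The concern.** The audit effect is a change within HCPs. A model with only an HCP intercept lets HCPs differ in their starting rate but not in how much they change. The intervention described in the multifaceted-intervention section and Table 3 makes unequal change plausible: feedback is individual, goals are set by the participants, and waiting-room posters would be shared by colleagues at one site. If change does vary, the model omits a component of variance that does not shrink with the number of cases, and the confidence interval and P value for the audit effect are too favourable.

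The named fit check would not reveal this. A Wald test of the model asks whether the coefficients are zero. It can be highly significant whether or not the random part is right.

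Separately, a correlation described as belonging to the practice is used in a calculation whose clusters are HCPs. If several participants share a site and 0.1 holds across the site, the design effect is larger than the one used.

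**Working it through.** **1. Reproducing the 25 HCPs.** Inputs from the statistical section: 40% and 25%, two-sided 5%, 80% power, 25 cases per HCP, correlation 0.1.

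- Cases per audit without clustering: n = [1.96·√(2·0.325·0.675) + 0.842·√(0.24 + 0.1875)]² / 0.15² = 152 (165 with continuity correction).
- Design effect with the HCP as cluster: 1 + (25 − 1)·0.1 = 3.4.
- HCPs needed: 152·3.4/25 = 20.7, so 21. With continuity correction, 165·3.4/25 = 22.4, so 23.
- Power at 25 HCPs: effective n = 625/3.4 = 184 per audit, power 0.87.

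So 25 is adequate, with a small margin, when one HCP is one cluster and the two audits are treated as independent.

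**2. Applying 0.1 across a practice of h HCPs.** The document does not give h, so these values are assumed. Design effect = 1 + (25h − 1)·0.1. If the practice effect correlates r between audits (also assumed), pairing reduces the factor to 1 + (25h − 1)·0.1 − 25h·0.1·r.

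| h | Design effect (r = 0) | Power, r = 0 | Power, r = 0.5 | Power, r = 0.8 |
|---|---|---|---|---|
| 1 | 3.4 | 0.87 | 0.97 | 0.998 |
| 1.25 | 4.03 | 0.81 | 0.95 | 0.996 |
| 2 | 5.9 | 0.65 | 0.87 | 0.985 |
| 3 | 8.4 | 0.50 | 0.75 | 0.96 |
| 5 | 13.4 | 0.34 | 0.56 | 0.87 |

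Without credit for pairing, power drops below 0.80 once h exceeds about 1.25.

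**3. Size of the HCP-intercept model.** A random-intercept logistic model with the HCP level only was simulated with 25 HCPs, 25 cases per audit, two audits and no true effect (400 to 600 runs per scenario).

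*Stable practice and HCP effects, total correlation 0.1:* size was 4.5% to 5.2% for 1, 3 and 5 HCPs per practice. The reported and empirical standard errors agreed at about 0.12.

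*Change that varies between practices* (log-odds variance v, assumed; h = 1 is variation between HCPs):

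| h | v = 0.05 | v = 0.1 | v = 0.2 |
|---|---|---|---|
| 1 | 7% | 8% | 10% |
| 3 | 9% | 14% | 24% |
| 5 | 15% | 22% | 27% |

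The reported standard error stayed at 0.12 throughout, while the empirical one rose to between 0.13 and 0.23.

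*Closed-form check.* True variance ≈ 0.12² + v/(25/h), and size = 2·[1 − Φ(1.96·0.12/true SE)].

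- h = 1, v = 0.1: √(0.0144 + 0.004) = 0.136, size 8%.
- h = 1, v = 0.36: √(0.0144 + 0.0144) = 0.170, size 17% (about 16% by simulation).
- h = 3, v = 0.1: √(0.0144 + 0.012) = 0.162, size 15%.
- h = 5, v = 0.2: √(0.0144 + 0.04) = 0.233, size 31%. One set of runs gave 27% here, and a second simulation had an upper end of 31%.

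The ranges are therefore about 7-16% for variation between HCPs (v from 0.05 to 0.36) and about 9-31% for variation between practices of 3 to 5 HCPs (v from 0.05 to 0.2).

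**The case against.** Four points can be made for the plan.

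*A missing practice level does not by itself narrow the interval.* A reader might infer that it does. In a before-after contrast on the same HCPs, a stable practice effect cancels, and the simulation confirms correct size. This stands. The harm needs unequal change, which the document does not quantify.

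*The Wald test is not the only check.* A reader who stops at "Goodness of fit will be assessed using the Wald test of the model" might think so, but the sentence goes on to name a deviance test between alternative models, which is the right tool. This also stands. However, the article does not say that a model with varying change will be among the alternatives.

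*The study is not shown to be underpowered.* The article does not say that colleagues from one site enrol together, Table 1 also lists single-handed and individual practices, and "within-practice" may be loose wording for within-participant. The stated calculation takes no credit for pairing, which at r = 0.8 restores 0.87 even at 5 HCPs per practice. All of this stands and makes the power loss conditional.

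*Detail may be in the separate analysis plan, and the models are not the sole basis for inference.* The null hypothesis is assigned to a Fisher exact test, the models are introduced as an additional estimate, and "Data from all centres will be analysed together" fixes no pooled model. Random audit effects could be specified in the plan that is not shown. That limits the claim to what the article itself fixes: the two levels, the label on the correlation, and the Wald test as a measure of fit.

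**Conclusion.** The point holds in conditional form. With an HCP intercept only, the standard error of the audit effect is right if HCPs and practices all change alike and too small if they do not. The sizes in the working rest on assumed variances of change and assumed numbers of HCPs per practice, and on reading the two-level model as intercept-only. Part of the problem remains even with one HCP per practice.

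Calling a model Wald test a goodness-of-fit check is an error regardless of these assumptions.

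The 25-HCP figure delivers at least the stated 80% if practice and HCP nearly coincide, or if pairing offsets the larger cluster. Otherwise it may not. The document does not show which case applies, so the defect is an unresolved mismatch of units rather than a demonstrated shortfall in power.

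**What to change.** - Record a site code (practice, service, home or pharmacy) for each HCP. The data-management section keeps basic HCP information only while the study runs, so this is easiest to secure before then.
- Let the audit effect vary by HCP and by site, through random audit effects or through site-clustered standard errors with a small-sample correction.
- Drop the Wald test as the fit check. Use the deviance test already planned to compare models with and without these random effects.
- State whether 0.1 refers to the HCP or to the practice. Then either state that the 25-HCP figure assumes about one HCP per practice, or restate power for the expected number per practice with the assumed correlation between audits.

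The cost is one extra code per HCP and some wording. The intervals will be somewhat wider where change varies.
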